	Critical Thinking	Halpern Critical Thinking Assessment^1^, Heuristic and Biases items^2^	2	Critical thinking will increase more for the MM group than for the SM group from t_1_ to t_4_ *(a* ^*1,2*^ *)* and this effect will be moderated by baseline endorsement of thinking dispositions *(b* ^*1,2*^ *)*	Mixed ANOVA, ANCOVA
	Thinking Dispositions	Actively Open-minded Thinking^1^, Need for Cognition^2^	3	Endorsement of critical thinking dispositions will increase more for the MM group than for the SM group from t_1_ to t_4_ *(a* ^*1,2*^ *)*	Mixed ANOVA
	Executive Control	Sternberg Working Memory Task	4	Executive control will increase more for the MM group than for the SM group from t_1_ to t_4_ *(a)* and this increase will mediate the relationship between levels of mindfulness and critical thinking performance following the intervention *(b)*	Mixed ANOVA, SEM
Secondary	Wellbeing	Warwick-Edinburgh Mental Wellbeing Scale	5	Wellbeing will increase and negative affect will decrease more for the MM group than for the SM group from t_1_ to t_4_	Mixed ANOVA
	Positive Affect and Negative Affect	Positive Affect and Negative Affect Schedule subscale	6	Positive affect will increase more for the MM group than for the SM group from t_1_ to t_4_ *(a)*	Mixed ANOVA
	Real-world Outcomes	Real-world Outcomes Inventory	7	Negative real-world outcomes will decrease more for the MM group than for SM group from t_1_ to t_4_	Mixed ANOVA
Manipulation Checks	Meditation Quality	Practice Quality-Meditation	8	Meditation quality will be positively associated with increases in mindfulness *(a)*, executive control *(b)* and critical thinking *(c* ^*1,2*^ *)* and meditation quantity *(d)*, task enjoyment *(e)* and task difficulty *(f)* and it will be higher in the MM group and across time.	Correlation, Mixed ANOVA
	Meditation Quantity	Total Minutes Spent Meditating	9	Meditation quantity will be positively associated with increases in mindfulness *(a)*, executive control *(b)* and critical thinking *(c* ^*1,2*^ *)* and meditation quality *(d)*, task enjoyment *(e)* and task difficulty *(f)* and will not differ across time or groups.	Correlation, Mixed ANOVA

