	Task Enjoyment	Technology Acceptance Model Questionnaire subscale	10	Task enjoyment will be positively associated with increases in mindfulness *(a)*, executive control *(b)* and critical thinking *(c 1,2*) and meditation quality *(d)*, meditation quantity *(e)* and task difficulty *(f)* and will not differ across time or groups.	Correlation, Mixed ANOVA
	Task Difficulty	Technology Acceptance Model Questionnaire subscale	11	Task difficulty will be positively associated with increases in mindfulness *(a)*, executive control *(b)* and critical thinking *(c 1,2*) and meditation quality *(d)*, meditation quantity *(e)* and task difficulty *(f)* and will not differ across time or groups.	Correlation, Mixed ANOVA
	Intervention Acceptability	Items from Kirkpatrick et al. [60]	12	Intervention acceptability will be positively associated with increases in mindfulness *(a)*, executive control *(b)* and critical thinking *(c* ^*1,2*^ *)* and meditation quantity *(d)*, task enjoyment *(e)* and task difficulty *(f)* and it will be higher in the MM group but will not differ across time.	Correlation, Mixed ANOVA
	Attrition	No. of participants lost from baseline to t_4_	13	Attrition will be negatively associated with meditation quality *(a)*, meditation quantity *(b),* task enjoyment *(c)* and task difficulty *(d)* and will not differ across time or groups.	Correlation, Mixed ANOVA

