## Methods/design

### Design

The CONSORT guidelines for evaluation of randomised controlled trials [45], the CONSORT extension for non-pharmacological treatment interventions [46], the SPIRIT checklist of protocol items and the TIDIER checklist for intervention description and replication [47] were adhered to in the design of this study and this protocol paper.

This study involves a two-arm randomised-controlled superiority trial with one intervention condition, guided mindfulness meditation, and one active-control condition, sham meditation. The design employed is a 2 (condition) X 2 (time) parallel-group design which is explanatory in nature. Measurement will take place at baseline (i.e. before randomisation, T1) and 6 weeks after baseline (T4). The delivery of the content of both the intervention condition and the active-control condition will take place between T1 and T4. Manipulation checks will be carried out to assess intervention acceptability, technology acceptance and meditation quality 2 weeks after baseline (T2) and 4 weeks after baseline (T3). See Table 2 for a description of the procedure.

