### Adherence

Objective adherence data will be collected through the Headspace accounts of the participants. These data will include both the number of sessions initiated and the number of minutes spent listening to the guided sessions. One email and one text message per week will be sent to participants to encourage them to adhere to the intervention.

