## Discussion

This study aims to investigate the claim that mindfulness practice facilitates critical thinking. It will also test whether executive function mediates the relationship between mindfulness and critical thinking in line with default interventionist theory, previous cross-sectional studies which examined this relationship, and previous experimental studies which suggested this relationship [12–17]. It will achieve this aim by randomising participants to either an experimental condition involving the learning of mindfulness meditation or an active-control condition involving guided sham meditations which will both be delivered through the same online application, Headspace. Dispositional mindfulness, executive function and critical thinking will be assessed at baseline and following the end of the intervention along with measures of intervention adherence, wellbeing, thinking dispositions and real-world outcomes of critical thinking. Manipulation checks assessing intervention acceptability and meditation quality will also be administered.

This study has many strengths. It is pre-registered with the ISRCTN registry which is openly accessible. The use of an active-control which is identical in expectations (which will be measured) and presentation (i.e. through the Headspace application and by [name], a trained Buddhist monk) represents an advance from the usual attention or waitlist controls employed in previous mindfulness meditation interventions [10]. Another advance is the use of objective measures of intervention adherence. Where most previous studies have relied on self-report measures of adherence (when included), the application used to deliver the intervention materials in this study will also track the amount of guided meditations participants engage in and for how long they engage with them. Finally, participants will be allocated to their respective groups without knowing which was the experimental condition and this information will also be kept from the primary researcher until after data analysis is complete in order to ensure a double-blind RCT design.

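### Table 1 assigns a mixed ANOVA and an across-time claim to attrition (H13), and likewise to total minutes (H9), but each is defined as a single total, so the time part cannot be tested as written

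*Protocol article*

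**What the plan says.** Table 1 (under The current study) gives each hypothesis a measure, a statement and an analysis.

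- **Row 13, attrition.** The measure is "No. of participants lost from baseline to t_4". The hypothesis closes "and task difficulty *(d)* and will not differ across time or groups". The analysis entry is correlation and mixed ANOVA.
- **Row 9, meditation quantity.** The measure is "Total Minutes Spent Meditating". The hypothesis closes "and will not differ across time or groups", with the same analysis entry.

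Other sections bear on whether either variable is repeated over time.

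- **Design**, on the outcomes: "Measurement will take place at baseline (i.e. before randomisation, T1) and 6 weeks after baseline (T4"). On the interim checks: "Manipulation checks will be carried out to assess intervention acceptability, technology acceptance and meditation quality 2 weeks after baseline (T2"), and again at week 4 (T3). Neither attrition nor minutes is in that list.
- **Adherence**, on the app data: "These data will include both the number of sessions initiated and the number of minutes spent listening to the guided sessions". The Discussion adds that the app "will also track the amount of guided meditations participants engage in and for how long they engage with them". Neither says whether the records are dated or will be split by period.
- **Statistical analysis** spells out one mixed ANOVA, pre/post by group, for the outcome measures. For the manipulation checks it names correlations.

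**The concern.** A mixed ANOVA with a time factor compares scores taken on the same person at two or more times. Attrition as defined in row 13 is one binary result per participant, known at T4. It has no second value to compare with, and it is not a continuous score. The measure, the claim and the analysis in that row do not fit together.

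The row matters because the Discussion says the mindfulness sessions may prove more engaging than the sham sessions, and that attrition may then differ between arms. Row 13 is the only stated test of that. Missing data are to be handled by carrying the baseline observation forward, which sets the change of a lost participant to zero. Unequal loss would therefore feed directly into the estimated difference in change, so the check on it should be analysable as written.

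Row 9 has the same mismatch: a single sum per participant has no time factor either.

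**Working it through.** The plan gives no figure to reproduce on this point. The check is mainly a comparison of the text, with a small illustration.

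**Step 1: what each stated measure yields.**

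| Row | Stated measure | Values per participant | Time factor |
|---|---|---|---|
| 13 | Number lost, baseline to T4 | one (lost: yes/no) | none |
| 9 | Total minutes | one (a sum) | none |

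**Step 2: whether another section supplies the repeated values.** The T2/T3 list in Design covers acceptability, technology acceptance and meditation quality only. The pre/post ANOVA in Statistical analysis cannot help, because neither variable has a meaningful pre-intervention value: nobody has been lost and nobody has used the programme. Adherence and Data collection describe minutes and sessions without periods. So no section shown supplies a within-participant series for either variable.

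**Step 3: what happens if a time series is constructed.** The answer depends on how it is built, and the article does not say. Inputs: 20% attrition and 78 recruited (Sample size), taken as 39 per arm. Three two-week windows, with loss spread evenly over them, are an assumption.

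- *Loss per interval, or running loss.* At a constant risk per window, h = 1 − 0.8^(1/3) = 0.0717. Of 78, the losses are 5.6, 5.2 and 4.8 per window, summing to 15.6 = 0.20 × 78. The running total is 5.6, 10.8, 15.6. Per-interval loss is nearly flat, while the running total must rise.
- *Simulated mixed ANOVA time effect, equal loss in both arms* (4,000 runs). With 0/1 coding of loss in each interval it is significant in 5.2% of runs, which is the nominal level. With 0/1 coding of loss so far it is significant in 99.4%.
- *Minutes at a constant rate of practice* (2,000 runs, 30 per arm; assumed mean 70 per window, between-person SD 25, within-person SD 30). With minutes per window the time effect is significant in 4.4% of runs; with running totals from the same data, in 100%.

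The time claim is therefore coherent and can be true under per-interval coding, and is rejected almost every time under cumulative coding. As written it specifies neither.

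**Step 4: the between-arm part.** With per-interval coding, a participant's mean over the three windows is D/3, where D = 1 if lost by T4 and 0 otherwise. The arm effect is then the same test as a two-group comparison of D. So the arm comparison does not need the repeated-measures model, and a direct comparison of proportions answers it.

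**Step 5: precision of the direct comparison.** At 20% loss in each arm, the 95% CI half-width is 1.96 × √(2 × 0.2 × 0.8 / 39) = 1.96 × 0.0906 = 0.178, about 18 percentage points. The article gives 38 per group but 78 in total; with 38 the half-width is 0.180, so the choice does not matter here.

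**The case against.** The strongest defence has four parts.

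1. **The natural reading is per period.** A claim of no difference across time would ordinarily mean the amount in each period, and under that coding the ANOVA behaves acceptably. This stands as a reason not to call the hypothesis false. It does not supply the missing definition, since row 13 fixes one count over the whole span.
2. **Minutes may be divisible.** The content is 30 separate ten-minute sessions and the app tracks sessions and duration. Nothing excludes minutes per period, and the between-arm comparison of total minutes is unaffected. This stands, and it makes the H9 part the weaker half.
3. **The article is condensed.** The timeline in Table 2 is not shown, the same analysis entry appears in all six manipulation-check rows, and windows are commonly fixed in a full protocol or analysis plan. This explains the looseness. It does not remove the mismatch in row 13, where the article itself fixes a measure and an analysis that do not fit.
4. **Nothing primary depends on it.** True, and the severity reflects that.

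A reader might go further and infer that both hypotheses fail by construction because loss and minutes can only accumulate, so the time effect would always be rejected and the arm comparison would lose power. The documents do not support this. It requires running totals, which the article never mentions; Step 3 shows the automatic rejection disappears with per-interval coding, and Step 4 shows that the arm comparison then loses nothing. With no repeated measure defined, the time claim is undefined, which is different from false.

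**Conclusion.** The point holds in a limited form. Row 13 assigns a repeated-measures analysis and an across-time claim to a variable defined once per participant. That analysis cannot be run on that measure, and the across-time part is untestable as written. Row 9 has the same gap for total minutes, less seriously, because period data may exist.

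The group comparisons in both rows remain possible, as do the H9 correlations. No primary or secondary outcome and no sample size depends on either row, so the severity is low. What raises it above mere wording is that row 13 is the only stated test of differential attrition.

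The conclusion rests on the text shown. It would fall away for H9, and narrow for H13, if Table 2 or a fuller plan defines loss and minutes by period. The simulations only show that the coding decides the result; their windows, even spread of loss and minutes parameters are assumptions.

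**What to change.** **H13.** Replace the mixed ANOVA with the difference between arms in the proportion lost by T4, with its 95% CI and a two-group test of proportions. Describe the time of loss by arm, per interval or with a Kaplan–Meier curve. Delete the across-time clause. Report the interval prominently: at about ±18 percentage points, a non-significant test would not show that attrition was equal.

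**H9.** Compare total minutes between arms in one two-group comparison. For the time claim, either define minutes per period (for example weeks 1–2, 3–4 and 5–6) and apply the mixed ANOVA to those, or drop the across-time clause.

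**Cost.** A change of wording in two rows of Table 1 and a simpler analysis. H13 needs no new data for the arm comparison; describing the time of loss needs the date or interval of each loss. The per-period option for H9 depends on the app records being dated, which should be confirmed with the app provider before the clause is kept.

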### Sample size (Incl. flow chart)

The statistical program G*Power was used to conduct power analysis in order to determine the appropriate sample size. Adhering to Cohen’s [48] guidelines for small (*r* = 0.1), medium (*r* = 0.3), and large (*r* = 0.5) effects, two-tailed alpha of .05 was assumed for all tests. With 2 groups, 6 measurements, an assumed correlation among repeated measures of 0.3 (typically low in such research; [49]) as well as a medium effect size (again typical in research on the cognitive effects of mindfulness; [10]) and a power of 0.8, the recommended sample size for mixed (repeated-measures and between factors) ANOVA was 56. As it is recommended that the sample size be a multiple of the number of measurements, a sample of at least 60 will be sought, 30 per group. Because of an anticipated attrition rate of 20 %, 38 participants are required per group i.e. 78 in total. Previous studies using Headspace have reported attrition rates between 20 and 40 % [41, 44]. We expect an attrition rate closer to 20 % because of the incentives in the form of course credit, lunches provided at data collection and free subscription to Headspace for 6 months following the intervention.

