### Intervention

Intervention materials will be delivered via Headspace, a commercially available application which runs on all major smartphones, tablets and web browsers. The Headspace meditation scripts are designed by an individual with Buddhist monastic training who guides users through mindfulness meditations and key concepts related to mindfulness meditation using both audio and visual materials. In order to participate, individuals are required to have access to a smartphone or desktop computer with Internet access. Headspace makes meditating accessible by combining technology and simple techniques that are designed for new meditators. Participants can practice at any time of day wherever they prefer. Headspace offers straightforward, guided, bite-sized mindfulness training that is non-religious. We have signed guarantees with Headspace that participant data collected through Headspace will never be sold, distributed, or publicised (except anonymously in scientific publications with Headspace having no involvement in the conduct, analysis, or reporting of the research in any way).

Participants will be sent an email introducing Headspace and describing the sign-up process. To get started, participants are required to register on headspace.com using their name and email address. Each participant will be given a unique code providing free access to Headspace for the duration of the study. After registering, participants may begin meditating straight away.

The proposed intervention is 6-weeks in length. All participants will be encouraged to practice meditation/sham-meditation daily for the course of the 6-weeks by listening to each of the 30 ten-minute guided sessions which they will access through the Headspace app. The nature of the sessions they can access depends on the group they are assigned to.

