### Manipulation checks

In week 2 and week 4 participants will complete short questionnaires assessing mindfulness meditation quality and task expectations, enjoyment and difficulty. These will be completed online, allowing participants to complete them at their convenience. Participants will be asked to complete these measures directly following a meditation session.

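### Hypothesis 13(b) correlates dropout with total minutes meditated, a total that leaving can itself cut short, so the predicted negative association can appear when practice has no bearing on who leaves

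*Protocol article*

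**What the plan says.** Everything here is in the protocol article.

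- **Outcome.** Table 1, row 13 measures attrition as "No. of participants lost from baseline to t_4".
- **Prediction.** The row states that "Attrition will be negatively associated with meditation quality" (part a), then continues with "meditation quantity *(b),* task enjoyment *(c)* and task difficulty *(d)* and will not differ across time or groups". The analyses listed are correlation and mixed ANOVA.
- **Predictor in part (b).** Row 9 measures meditation quantity as "Total Minutes Spent Meditating". Under Adherence, the Headspace account supplies "the number of minutes spent listening to the guided sessions".
- **Content available.** Under Intervention, participants are encouraged to practise daily for six weeks by "listening to each of the 30 ten-minute guided sessions", that is 30 × 10 = 300 minutes.
- **Predictors in parts (a), (c) and (d).** Quality, enjoyment and difficulty are questionnaire scores from weeks 2 and 4. Under Manipulation checks, "Participants will be asked to complete these measures directly following a meditation session".
- **Test level.** Under Sample size, "two-tailed alpha of .05 was assumed for all tests".

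Nowhere does the article limit minutes to a period before loss, divide them by time in the study, or plan a time-to-dropout analysis.

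**The concern.** Total minutes build up over the same six weeks in which participants can be lost. For anyone who leaves and stops using the app, the outcome shortens the predictor. The correlation then mixes two things: whether people who practise less are more likely to leave, and the fact that people who have left practise less afterwards. Only the first is informative about engagement and dropout.

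The hypothesis is pre-specified and directional, and the mechanical part has the predicted sign. A significant result could therefore be reported as support for H13(b), and read as evidence that low practice goes before dropout, when the data carry no such evidence.

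**Working it through.** **The plan's own figures.** The article gives no power or expected correlation for H13, so there is no stated figure to reproduce. Sample size supplies the recruitment total (78), the expected attrition (20%, with 20 to 40% reported earlier) and the two-sided 0.05 level. That section also gives 38 per group, which is 2 × 38 = 76. Running one scenario with 76 gives -0.43 and 98% significantly negative, so the difference does not matter here.

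**Assumptions not in the article.** These are the day of leaving, whether leavers stop using the app, and how daily practice varies between people. Each person has a daily practice probability drawn independently of loss, so the true relation is zero. One ten-minute session is modelled per practice day, capped at 30 sessions. One a day is a modelling choice; the article sets no daily limit.

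**Formula.** With a yes/no outcome, r = (mean among lost − mean among retained) × √[p(1 − p)] / SD. At p = 0.20, √(0.2 × 0.8) = 0.4. For 78 participants the critical t on 76 df is 1.99, so r is significant beyond 1.99/√(76 + 1.99²) = 0.22 in absolute value.

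**Hand check, cap ignored.** Take practice probability q from Beta(2,2), with mean 0.5, variance 0.05, E[q(1 − q)] = 0.20 and E[q²] = 0.30. Leavers stop at a uniform time over 42 days.

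- Retained: mean 42 × 0.5 = 21 sessions; variance 42 × 0.20 + 42² × 0.05 = 96.6.
- Lost: mean 21 × 0.5 = 10.5 sessions; variance (21 × 0.20 + 588 × 0.30) − 10.5² = 70.35, where 588 = 42²/3.
- Overall variance: 0.8 × 96.6 + 0.2 × 70.35 + 0.16 × 10.5² = 109.0, so the SD is 10.44.
- r = −10.5 × 0.4 / 10.44 = −0.40, well beyond 0.22 although practice and loss are unrelated.

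**Simulation with the cap.** N = 78, 20% loss, practice probabilities from Beta(2,2), (4,4), (3,6) and (1,1). Ranges are across the four distributions.

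| Pattern of loss | Mean r | Significantly negative |
|---|---|---|
| All leavers stop, evenly over 42 days | -0.34 to -0.50 | about 88-99% |
| Half of leavers stop, evenly over 42 days | about -0.2 (-0.17 to -0.27) | about 34-65% |
| All stop, only in weeks 5-6 | -0.10 to -0.19 | 13-39% |
| None stop; they only miss T4 | 0.00 | 2-3% |

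The nominal rate in the negative tail is 2.5%.

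A more skewed, lower practice distribution, Beta(0.8,1.6), weakens the effect: -0.27 (73%) for even loss and -0.08 (9%) for loss in weeks 5-6. At 40% even loss the mean r is -0.50 (99.8%).

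**The alternative.** Using minutes in days 1-14 among those still in the study at day 14, related to later loss, the mean r is 0.00 and 2-3% are significantly negative. Events remaining at 20% even loss: 0.20 × 78 × 28/42 = 10.4, about 10.

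**Parts (a), (c) and (d).** These are scores at two time points, not running totals, so the arithmetic above does not apply. A participant who stopped before week 2 has no score, and the text schedules no baseline value for these measures that could be carried forward. The correlations therefore describe only people still practising at week 2.

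**The case against.** The strongest reply is that loss and app use are recorded separately. Loss means missing an assessment held in the School's PC suites, while minutes come from the Headspace account, and access runs for the whole study. Someone who only misses T4 can keep logging minutes, and if all losses were of that kind there would be no bias. This stands, and it is why the point is conditional. A reader might infer that the negative result is guaranteed whatever the data; the article does not support that.

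A second reply is that H13 speaks of association, not prediction. That is fair: as a bare statement that leavers log fewer minutes, H13(b) would not be false. It would, however, say little about why people leave.

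A third is that the choice of window belongs in a fuller analysis plan. Row 9's prediction that quantity will not differ across time does imply minutes by period. But rows 9 and 13 together already fix the outcome, the predictor, the sign and the method, so this is a stated test and not an omitted detail.

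Two further readings are tempting and should be resisted. The Discussion's worry that a less engaging sham could lead to differing attrition is about rates between arms; it neither uses nor depends on H13(b). And no analysis can give week-2 scores to people who left before week 2, so parts (a), (c) and (d) need a statement of scope, not a repair.

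**Conclusion.** The point holds for H13(b) in conditional form. Where leavers also stop using the app, total minutes are shortened by the outcome, and the planned correlation tends towards the predicted sign with no true relation. The bias runs from none, if leavers only miss T4, to near-certain false confirmation, if all stop at evenly spread times. Even if only half stop, about a third to two thirds of trials would be significantly negative, against a nominal 2.5%. Where the trial would fall in that range cannot be settled from the article, because it gives neither the timing of loss nor leavers' app use.

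The consequence is limited. H13 is a manipulation-check hypothesis; the primary and secondary comparisons between groups and the sample size do not rest on it.

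**What to change.** In H13(b), replace total minutes with app-logged minutes in a fixed early window, for example days 1-14. Relate these to loss after that window among participants still in the study at its end. State in advance how being still in the study at day 14 is determined: if people who have silently stopped are counted as present, some of the shortening returns. Describe earlier leavers separately, by number and arm. For (a), (c) and (d), add one sentence saying that the result applies to participants still practising at week 2.

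The change is to wording and needs no new data, provided the app log can be split by date, as row 9's comparison across time already requires. The cost is fewer events: about 10 at 20% even loss, and none if everyone leaves within 14 days. The estimate will be imprecise, so a simple correlation or a one-predictor model is preferable to a larger one.
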